## Abstract

**Background:**

Patients with metastatic spinal cord compression (MSCC) and favorable survival prognoses can benefit from radiation doses greater than 30Gy in 10 fractions in terms of improved local progression-free survival (LPFS) and overall survival (OS).

**Methods/design:**

This prospective study mainly investigates LPFS after precision radiotherapy (volumetric modulated arc therapy or stereotactic body radiotherapy) with 18 × 2.33Gy in 3.5 weeks. LPFS is defined as freedom from progression of motor deficits during radiotherapy and an in-field recurrence of MSCC following radiotherapy. The maximum relative dose allowed to the spinal cord is 101.5% of the prescribed dose, resulting in an equivalent dose in 2Gy-fractions (EQD2) for radiation myelopathy is 45.5Gy, which is below the tolerance dose of 50Gy according to the Quantitative Analyses of Normal Tissue Effects in the Clinic (QUANTEC). The EQD2 of this regimen for tumor cell kill is 43.1Gy, which is 33% higher than for 30Gy in 10 fractions (EQD2 = 32.5Gy). Primary endpoint is LPFS at 12 months after radiotherapy. Secondary endpoints include the effect of 18 × 2.33Gy on motor function, ambulatory status, sensory function, sphincter dysfunction, LPFS at other follow-up times, overall survival, pain relief, relief of distress and toxicity. Follow-up visits for all endpoints will be performed directly and at 1, 3, 6, 9 and 12 months after radiotherapy. A total of 65 patients are required for the prospective part of the study. These patients will be compared to a historical control group of at least 235 patients receiving conventional radiotherapy with 10x3Gy in 2 weeks.

**Discussion:**

If precision radiotherapy with 18 × 2.33Gy results in significantly better LPFS than 10x3Gy of conventional radiotherapy, this regimen should be strongly considered for patients with MSCC and favorable survival prognoses.

**Trial registration:**

Clinicaltrials.gov NCT04043156. Registered 30-07-2019.

## Background

A considerable number of patients irradiated for metastatic spinal cord compression (MSCC) have a favorable survival prognosis with 6-month and 12-month survival rates of > 80 and > 70%, respectively [1, 2]. These patients are easily identified using validated prognostic tools [1, 2] and can live long enough to develop a recurrence of MSCC in the irradiated part of the spine. In case of such an in-field recurrence, many patients are not suitable for surgery [3, 4]. Moreover, safe administration of a second course of radiotherapy is often taking into account the risk of radiation myelopathy [5]. Longer-course radiotherapy programs (2–4 weeks) can result in better local control and local progression-free survival (LPFS) than short-course programs [6, 7]. In a retrospective matched-pair study, local control and LPFS were further improved with doses beyond the most commonly used longer-course regimen 30Gy in 10 fractions (10x3Gy) [8]. Increase of the dose for MSCC is limited by the radiation tolerance of the spinal cord [9, 10]. With precision radiotherapy techniques such as volumetric modulated arc therapy (VMAT) and stereotactic body radiotherapy (SBRT), radiation doses can be further increased than with conventional radiotherapy [11].

In the RAMSES-01 study, precision radiotherapy with 18 × 2.33Gy in 3.5 weeks is investigated. The equivalent dose in 2Gy-fractions (EQD2) of this regimen for tumor cell kill is 43.1Gy, which is 33% higher than for 30Gy in 10 fractions (32.5Gy) [12, 13]. The EQD2 of 18 × 2.33Gy for radiation myelopathy is 45.5Gy, which is below the tolerance dose of the spinal cord of 50Gy according to the Quantitative Analyses of Normal Tissue Effects in the Clinic (QUANTEC) [9]. The EQD2 of 18 × 2.33Gy for damage to the vertebral bone is 45.1Gy, which is below the tolerance dose of bone of 52Gy [9, 10]. Thus, precision radiotherapy with 18 × 2.33Gy can be considered safe.

This study includes two parts, a single-arm trial of patients receiving 18 × 2.33Gy and a comparison of this cohort to a historical control group treated with 10x3Gy. It aims to show that 18 × 2.33Gy of precision radiotherapy results in significantly better LPFS than 10x3Gy of conventional RT. If such superiority is shown, 18 × 2.33Gy could be recommended for patients with favorable survival prognoses.

## Methods/design

### Endpoints of the study

The primary endpoint is the 12-month LPFS following 18 × 2.33Gy of VMAT (preferred) or SBRT (possible for a single vertebra) in patients with favorable survival prognoses according to a validated score [1, 2]. This survival score is used by many physicians worldwide when aiming to assign the appropriate radiation regimen to a patient with MSCC.

### Study design

The first part of this study represents a single-arm trial and evaluates the effect of precision radiotherapy with 18 × 2.33Gy given over 3.5 weeks on LPFS. Sixty-five patients (62 patients + 5% for drop-outs) are supposed to be recruited within 21 months. The characteristics to be recorded to allow a comparison with the historical control group include age, gender, primary tumor type, interval between tumor diagnosis and MSCC, number of vertebrae affected by MSCC, additional bone or visceral metastases, time developing motor deficits, pre-radiotherapy ambulatory status, and performance status according to the Eastern Cooperative Oncology Group (ECOG) [7]. Propensity score techniques will be applied to reduce confounding due to differences between the historical control group and prospective trial data [14]. The inclusion and exclusion criteria are almost identical to those of a previous trial investigating 5x5Gy of precision radiotherapy of MSCC [11]. Only the inclusion criteria are supplemented by favorable survival prognosis (defined as 36–45 points on a survival score) [1, 2].

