### Assessments

The following endpoints will be prospectively assessed by the participating physicians directly and at 1, 3, 6, 9 and 12 months after radiotherapy and recorded in a case report form (CRF): Motor function, ability to walk, sensory function, sphincter dysfunction, LPFS, overall survival (OS), pain relief, relief of distress, and toxicity. If a recurrence of MSCC is clinically suspected (deterioration of motor function following improvement or no change of motor function during radiotherapy), MRI will be performed. For MRI, rates of sensitivity, specificity and diagnostic accuracy regarding the detection of MSCC of 93, 97, and 95%, respectively, were reported [16, 17]. In case of an out-field recurrence of MSCC, the patient will be censored for LPFS. Assessment directly after radiotherapy will result in a difference of one and a half week between the prospective cohort and the historical control group. However, this way of assessment was selected, since the primary endpoint LPFS included no progression of motor deficits during radiotherapy (=immediate response), which would ideally be assessed directly after the end of radiotherapy. Motor function will be evaluated with a 5-point scale [11, 18]. Sensory function will be assessed as absent, impaired or normal, sphincter dysfunction as yes or no [19]. For assessment of pain, a numeric self-assessment scale will be used (0–10 points) [20]. Distress will be evaluated with the distress thermometer (0–10 points [21, 22]. For assessment of toxicity, the Common Terminology Criteria for Adverse Events version 4.03 will be used [23].

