### Comparisons with the historical control group

The patients receiving 18 × 2.33Gy will be compared to historical control group of patients with a favorable survival prognosis treated with 10x3Gy of conventional radiotherapy from an anonymized database. Patients of the control group must fulfil the same inclusion and exclusion criteria as the patients of the prospective part of the study. It is estimated that 235 patients will qualify for the control group. To reduce the risk of hidden selection biases, a propensity score approach including 10 potential prognostic factors will be used for comparisons between the prospective cohort and the historical control group [7, 11].

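### The ten factors named for the propensity score leave out the pre-radiotherapy motor grade, although one of the two LPFS components is motor progression from that starting point

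*Protocol article*

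**What the plan says.** The Abstract (Methods/design) gives the primary endpoint two components: "LPFS is defined as freedom from progression of motor deficits during radiotherapy and an in-field recurrence of MSCC following radiotherapy". Assessments confirms the first: "the primary endpoint LPFS included no progression of motor deficits during radiotherapy (=immediate response". The same section states "Motor function will be evaluated with a 5-point scale" and lists motor function and ability to walk as separate items. It also makes motor function the trigger for the MRI that detects recurrence, namely "deterioration of motor function following improvement or no change of motor function during radiotherapy".

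Study design names the characteristics recorded for the historical comparison: "age, gender, primary tumor type, interval between tumor diagnosis and MSCC, number of vertebrae affected by MSCC, additional bone or visceral metastases", followed by "time developing motor deficits, pre-radiotherapy ambulatory status, and performance status according to the Eastern Cooperative Oncology Group (ECOG". Comparisons with the historical control group then fixes the number: "a propensity score approach including 10 potential prognostic factors will be used for comparisons".

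**The concern.** The motor component is a change from a starting value. The usual first candidate for adjustment in a non-randomised comparison of such an outcome is that starting value, and here it is not in the named set. Walking status is a related but different measurement, and the article itself keeps the two apart.

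Starting grade can affect LPFS in two ways. It may carry prognostic information beyond walking status. It also limits who can fail: if progression is scored on the 5-point scale, the only motor instrument the article names, a patient already at the worst grade cannot record one. If the two cohorts differ in starting grade among patients with the same values of the ten factors, their LPFS can differ without any treatment effect, and the planned score would not remove that difference. This bears on the main conclusion, because superiority over 10x3Gy is to be shown only through this comparison.

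**Working it through.** **Step 1: is the grade really outside the set?** Counting the Study design list with bone and visceral metastases as two items, as the Discussion does for the earlier matched-pair study:

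- age, gender, tumor type, interval from diagnosis, number of vertebrae, other bone metastases, visceral metastases: 7
- time developing motor deficits, ambulatory status, ECOG status: 3

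7 + 3 = 10, the number stated for the propensity score. The list is introduced as what the characteristics include, so it is not formally closed, but the stated count leaves no place for an eleventh. Nothing else in the article adjusts for motor grade.

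**Step 2: inputs for the size** (Sample size calculation): 62 versus 235 patients, control 12-month LPFS 84%, target gain 12.5 points (96.5%), two-sided 5% Pearson chi-square, stated power 77.9%.

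**Step 3: the plan's own figure.** For 96.5% versus 84%, exact enumeration of this test gives power of 83.5%, and the pooled normal approximation gives 81.3%. The stated 77.9% is not reproduced. A gain of 12 points (96% versus 84%) comes close, at 78.3% and 76.0%. This is a separate matter and does not affect the present point.

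**Step 4: the shift.** At equal values of the ten factors,

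shift in LPFS = (difference between groups in the share with a given grade) × (difference in 12-month LPFS between grades).

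The documents give neither input. Assumed ranges are 10 to 30 points for the share and 6 to 12 points for LPFS:

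- smallest: 0.10 × 0.06 = 0.006, or 0.6 points
- largest: 0.30 × 0.12 = 0.036, or 3.6 points

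One trial patient is 1/62 = 1.6 points, so the largest shift is about 2.2 patients. The sign may be either.

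**Step 5: false-superiority rate.** With no treatment effect, sum Bin(x; 62, 0.84 + shift) × Bin(y; 235, 0.84) over all outcomes (x, y patients free of local progression) where the Pearson test gives p < 0.05 and favours the new regimen:

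| Assumed shift (points) | Chance of declaring superiority |
|---|---|
| -3.6 | 0.4% |
| -0.6 | 1.5% |
| 0 | 1.9% |
| +0.6 | 2.5% |
| +1.2 | 3.2% |
| +2.4 | 5.2% |
| +3.6 | 8.2% |

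The unadjusted test stands in for the propensity-score analysis, as it does in the article's own power statement. The nominal rate in one direction is 2.5%, so the smallest positive shift does not exceed it.

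**The case against.** The case against has several sound parts.

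- **Partial adjustment already exists.** Ambulatory status, ECOG status and time developing motor deficits are all in the score. The article gives neither the anchors of the 5-point scale nor the levels of ambulatory status. If the scale largely encodes walking, much of the grade is already covered. This stands, and it limits the point to residual confounding.
- **The controls may not have the grade.** A historical database can record response as improved, unchanged or worse without the starting grade. The ten factors match those of the earlier matched-pair study, which would fit a list set by what the controls offer. This stands, and it makes the remedy conditional.
- **Covariate choice could be left to the analysis plan.** This carries less weight: the article names the factors and fixes their number, so it is a stated choice that is being questioned.

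A reader might also infer stronger claims, which the documents do not support.

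- **That the bias favours the new regimen**, because treatment should start within 48 hours and trial patients may therefore enter with better grades. The article gives no corresponding interval for the controls. The floor at the worst grade would also work the other way: if trial patients start better, more of them are able to progress, which lowers LPFS on the new regimen.
- **That half of the endpoint is affected.** Motor progression is one of two components, but no split of events is given.
- **That two or three failures would produce a false positive.** With 38 of 235 control failures (235 × 0.16 = 37.6), 3 of 62 gives p = 0.021 and 4 of 62 gives p = 0.051. With no effect, 62 × 0.16 = 9.9 failures are expected, so a false positive needs about seven fewer. A margin of about two failures describes losing a true effect: the planned 96.5% implies 62 × 0.035 = 2.2.

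**Conclusion.** The omission is established from the text: ten named factors, a stated count of ten, and no pre-radiotherapy motor grade, for an endpoint with a component measured from that grade. The consequence is residual confounding of unknown size and direction. The range of 0.4% to 8.2% around 1.9% illustrates sensitivity and does not estimate the actual error. It rests on the assumed shifts of up to 3.6 points either way, on 84% LPFS in the controls, and on the simple chi-square test. A positive shift would raise the chance of a false claim; a negative one would lower it but could hide a real benefit. Not knowing the direction is itself a reason to adjust. The point deserves attention before the comparison is run, but it does not invalidate the design.

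**What to change.** Establish whether the control database holds the pre-radiotherapy grade on the 5-point motor scale.

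- **If it does:** add the grade to the propensity score, or use it in place of ambulatory status if the scale already encodes walking ability. Check balance on it after matching or weighting. Report the motor-progression component by starting grade, with patients at the worst grade shown separately because they cannot progress on the scale.
- **If it does not:** say so, and state that residual imbalance in starting motor function limits the superiority claim.

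The cost is at most one more term in a score fitted to 62 treated patients, taking ten factors to eleven; substitution adds no further factor. No extra patients, visits or changes to treatment are needed.

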### Treatment

Radiotherapy is administered with VMAT (or SBRT) with 2.33Gy per fraction up to 42.0Gy in 3.5 weeks. This regimen represents an EQD2 of 43.1Gy for tumor cell kill, which means an increase of the radiation dose by 33% compared to 10x3Gy in 2 weeks (EQD2 = 32.5Gy). The EQD2 for radiation myelopathy is 45.5Gy for 100% of the prescribed dose [12, 13]. An EQD2 of <50Gy is considered safe and estimated to be associated with a risk of radiation-related myelopathy of < 0.2% [9]. Treatment should be started as soon as possible, i.e. within 48 h after first presentation to a radiation oncologist.

The planning target volume (PTV) should include the involved vertebrae plus 1 cm above and below. The PTV should be covered by the 95%-isodose. The spinal cord should not receive more than 101.5% of the prescribed dose (EQD2 = 46.6Gy for radiation myelopathy, α/β = 2Gy). This maximum dose is estimated to be associated with a risk of radiation-related myelopathy of < 0.2% [9]. Both the EQD2 of the prescribed dose (45.1Gy) and the EQD2 of the maximum dose (46.1Gy, α/β = 2.5Gy) are below the tolerance dose of bone of 52Gy [9, 11]. The mean doses (EQD2) for esophagus, heart and lung must be <34Gy, <26Gy and ≤ 7Gy [9]. The patients should receive concomitant corticosteroids during radiotherapy [15, 16].

### Assessments

The following endpoints will be prospectively assessed by the participating physicians directly and at 1, 3, 6, 9 and 12 months after radiotherapy and recorded in a case report form (CRF): Motor function, ability to walk, sensory function, sphincter dysfunction, LPFS, overall survival (OS), pain relief, relief of distress, and toxicity. If a recurrence of MSCC is clinically suspected (deterioration of motor function following improvement or no change of motor function during radiotherapy), MRI will be performed. For MRI, rates of sensitivity, specificity and diagnostic accuracy regarding the detection of MSCC of 93, 97, and 95%, respectively, were reported [16, 17]. In case of an out-field recurrence of MSCC, the patient will be censored for LPFS. Assessment directly after radiotherapy will result in a difference of one and a half week between the prospective cohort and the historical control group. However, this way of assessment was selected, since the primary endpoint LPFS included no progression of motor deficits during radiotherapy (=immediate response), which would ideally be assessed directly after the end of radiotherapy. Motor function will be evaluated with a 5-point scale [11, 18]. Sensory function will be assessed as absent, impaired or normal, sphincter dysfunction as yes or no [19]. For assessment of pain, a numeric self-assessment scale will be used (0–10 points) [20]. Distress will be evaluated with the distress thermometer (0–10 points [21, 22]. For assessment of toxicity, the Common Terminology Criteria for Adverse Events version 4.03 will be used [23].

### Comparisons with the historical control group

The patients receiving 18 × 2.33Gy will be compared to historical control group of patients with a favorable survival prognosis treated with 10x3Gy of conventional radiotherapy from an anonymized database. Patients of the control group must fulfil the same inclusion and exclusion criteria as the patients of the prospective part of the study. It is estimated that 235 patients will qualify for the control group. To reduce the risk of hidden selection biases, a propensity score approach including 10 potential prognostic factors will be used for comparisons between the prospective cohort and the historical control group [7, 11].

### Sample size calculation

The primary aim is to evaluate the LPFS at 12 months after 18 × 2.33Gy using VMAT or SBRT and to show superiority to 10x3Gy of conventional radiotherapy.

With respect to tumor cell kill, the EQD2 of 18 × 2.33Gy is considerably higher (+ 33%) than the EQD2 of 10x3Gy (43.1Gy vs. 32.5Gy). In a previous study, the 12-month LPFS rate was 84% with 10x3Gy in 2 weeks [8]. An increase by 12.5 percentage points is considered clinically important. Sixty-two eligible patients are required for estimation of the 12-month LPFS with appropriate precision. The statistical power should be at least 80%. Assuming that 5% of the patients will not be eligible for the efficacy analysis, a total of 65 patients should be recruited for the prospective trial.

For the comparison of the prospective trial and the historical cohort group, propensity score methods will be used to reduce confounding due to differences between the two data sets. Assuming that this comparison is performed with a simple Pearson-Chi-Square test (two-sided significance level = 5%), the power will be 77.9%, if the data of 62 prospectively treated patients and the data of 235 patients serving as historical control group can be used. Since the historical control database is constantly growing, the power will likely be 80% or higher at the time of the final analyses.

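### The power figure assumes a known 12-month LPFS status for every patient; with the deaths that the protocol's own survival figures permit, the 80% target is not assured

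*Protocol article*

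**What the plan says.** **Endpoint.** The Abstract (Methods/design) states: "LPFS is defined as freedom from progression of motor deficits during radiotherapy and an in-field recurrence of MSCC following radiotherapy". Death is not among the failures. The Assessments section adds one censoring rule, for out-field recurrence, and does not mention death.

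**Survival.** The Background describes patients with "favorable survival prognosis with 6-month and 12-month survival rates of > 80 and > 70%, respectively". The Discussion reports the matched-pair study that also supplies the planning rate. There, 2-year LPFS was 90% (higher dose) and 68% (10x3Gy), and 2-year OS was 68% and 53%. LPFS above OS in both groups is possible only if deaths were not LPFS events.

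**Power.** The Sample size calculation takes as its control rate that "the 12-month LPFS rate was 84% with 10x3Gy in 2 weeks" and adds "An increase by 12.5 percentage points is considered clinically important". It asks for at least 80% power and states, for a two-sided 5% Pearson chi-square test, that "the power will be 77.9%, if the data of 62 prospectively treated patients and the data of 235 patients" can be used. It expects growth of the control database to bring this to 80% or more.

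**Loss.** The allowance raises 62 patients to 65: "Assuming that 5% of the patients will not be eligible for the efficacy analysis, a total of 65 patients should be recruited". Study design calls the same 5% drop-outs.

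**The concern.** A chi-square test on 12-month status needs a yes or no for each of the 62 + 235 patients. A patient who dies free of local failure at, say, month 7 has no observed 12-month LPFS status under this definition. Such deaths are expected in this population and may be several times more frequent than the 5% allowed for. A patient who dies can no longer be observed to fail locally. Deaths therefore reduce the number of observable local failures, on which power mainly depends.

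At stake is whether the design can be described as having about 78% power, rising to 80% or more, for its superiority claim.

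**Working it through.** **Inputs from the protocol article.** LPFS at 12 months 84% (control) and 84 + 12.5 = 96.5% (prospective); n = 62 and 235; two-sided 5%; 12-month OS above 70%; 2-year OS 68% and 53%.

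**Assumptions.** Constant hazards, and death independent of local failure. From 2-year OS, 12-month OS is √0.68 = 0.82 and √0.53 = 0.73, so about 18% and 27% die by month 12. The figure of 30% deaths is a ceiling taken from the Background.

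**Step 1: the stated figure, complete data.**
- Pooled rate: (62 × 0.965 + 235 × 0.84)/297 = 0.866.
- SE under no difference: √[0.866 × 0.134 × (1/62 + 1/235)] = 0.0486.
- SE under the alternative: √[0.965 × 0.035/62 + 0.84 × 0.16/235] = 0.0334.
- z = (0.125 − 1.96 × 0.0486)/0.0334 = 0.89, so power is 81.3%.
- Exact enumeration of the Pearson test gives 83.5%.

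The stated 77.9% is not reproduced. Losses are therefore measured from 81-84%.

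**Step 2: local failures observed once deaths occur.** With hazards f = −ln(LPFS) and d = −ln(OS), the 12-month cumulative incidence of local failure is f/(f + d) × [1 − exp(−(f + d))]. Here f = 0.0356 (prospective) and 0.1744 (control).
- 18% deaths in both groups, d = 0.198: 3.2% vs 14.6%, a difference of 11.4 points.
- 18% (prospective) and 27% (control), d = 0.198 and 0.315: 3.2% vs 13.8%, 10.6 points.
- 30% in both groups, d = 0.357: 2.9% vs 13.5%, 10.6 points.

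**Step 3: power with all patients kept.** The chi-square columns put the Step 2 rates into the Step 1 calculation. The log-rank column is simulated with deaths censored (25,000 trials per row, standard error about 0.3 points).

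| Deaths by month 12 (prospective/control) | Controls | Chi-square, normal approx. | Chi-square, exact | Log-rank |
|---|---|---|---|---|
| none | 235 | 81.3% | 83.5% | 82% |
| 18% / 18% | 235 | 75.7% | 78.6% | 78% |
| 18% / 27% | 235 | 70.0% | 73.1% | 78% |
| 30% / 30% | 235 | 71.0% | 74.1% | 74% |
| 18% / 18% | 400 | 79.8% | 82.2% | 81% |
| 30% / 30% | 400 | 75.0% | 78.0% | 77% |

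By exact enumeration the loss is 83.5 − 78.6 = 4.9 points at 18% deaths and 83.5 − 74.1 = 9.4 points at 30%. No propensity-score loss and no censoring for out-field recurrence is included, because the article gives no figure for either.

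**Step 4: leaving out patients who die event-free.** With 18%/27% deaths, the apparent control failure rate becomes 0.138/(0.138 + 0.84 × 0.73) = 18.4%, and the prospective rate 0.032/(0.032 + 0.965 × 0.82) = 3.9%. The difference grows from 12.5 to 14.5 points and simulated rejection is about 83%. This is no real gain in power: unequal mortality has enlarged the contrast.

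**The case against.** **The chi-square is a planning simplification.** The article introduces it as an assumption, makes 77.9% conditional on the data being usable, plans propensity methods for the comparison, and uses censoring language for LPFS. This stands. A reader might infer that the trial will test crude 12-month proportions; the article does not say so, and a SAP may settle how deaths are handled. The power figure and the expectation of 80% are, however, stated in the article itself.

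**The 5% is for ineligibility or drop-out, and a patient censored at death stays in the analysis.** This also stands: the sentence is not false. But it is the only loss allowed for, and the power figure beside it treats the remaining 62 as complete.

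**The death rates are uncertain.** Correct. The 18% is an interpolation from the cited study's higher-dose group, and 30% is an upper limit.

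**At 18% deaths, power is about the stated 77.9%.** True. The stated figure is not shown to be too high at that end of the range.

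**Some analyses keep power above 80%.** A Kaplan-Meier difference with unpooled Greenwood variance had simulated power of 89-91% with deaths censored. One therefore cannot say that power falls below target however deaths are handled. Like for like, that test also loses power (93.5% without deaths). It is slightly liberal (simulated type I error 5.8%), and it rests on about 62 × 0.035 = 2 prospective events. It is not the test named for the calculation.

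**A stronger reading is that power is only 60-70%.** Shrinking the groups to 43 vs 165 at unchanged rates does give about 61% (normal approximation). But that also discards local failures seen in patients who later died, whose status is known. The documents do not support it.

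**Conclusion.** The concern holds in a limited form. The power calculation assumes a known 12-month LPFS status for all 62 + 235 patients, while the endpoint leaves out death and the protocol's own survival figure permits up to 30% deaths by then. Against 81-84% with complete data, power is about 78% at 18% deaths and 74% at 30% for a log-rank test with censoring or a chi-square that keeps everyone. The chi-square drops to about 73% if deaths are 18% and 27%.

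Growth of the control database helps but does not secure the target: 400 controls give about 80-82% at 18% deaths in both groups and about 77-78% at 30%. The 80% target is therefore not assured; it is not shown to be out of reach.

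These sizes rest on constant hazards, independence of death and local failure, and unweighted comparisons. Severity is moderate, because neither the recruitment number nor the data to be collected needs to change.

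**What to change.** - Keep n = 65.
- Base the power on a method that keeps all treated patients and says how death before month 12 is handled: propensity-weighted cumulative incidence of local failure with death as a competing event, or weighted Kaplan-Meier or log-rank with censoring at death. Do not base it on a chi-square of 12-month status.
- Restate the power as a range over 12-month OS of 70-82%: roughly 74-78% with 235 controls for the log-rank or all-patients comparison, before weighting. If another estimator is chosen, give its own figure and check its type I error.
- Qualify the expectation of 80% or more by stating the control number and the survival under which it is reached.
- State that the 5% covers ineligibility or drop-out only, not deaths.

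The cost is wording, a recalculation and a less favourable power figure. No further patients or data are needed, since OS is already assessed at every follow-up.
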